### Conventional Care Service (Control Group)

Participants randomized to the control group are offered to receive the standard municipal secondary or tertiary preventive care service. A recent study aimed at examining Danish municipal weight loss care services and identifying and describing their content and structure found 234 different municipal weight loss care services. Although they were different, they most frequently contained information about diet and physical activity. They also sometimes included information about how to develop healthy habits, and a few of the care services even included the promotion of well-being and social participation [32]. The standard municipal care service within the control group is therefore not the same, but none of the care services resembled the LIVA 2.0 program. At follow-up measurements, the control group participants were asked to describe if they had participated in any interventions since baseline, and if so, describe the content of these interventions. This enabled a qualitative assessment and summary of the standard care services used in the control group.

### Outcome Measures

Measurements are conducted by the health coach at baseline and at the 6-, 12-, and 24-month follow-ups. Data from national registers are collected before baseline and up to 3 years after the end of the intervention. Measurements are collected in a facility provided by the local municipality, the local general practitioner, or the clinical research center. Participants are scheduled for appointments by phone and with confirmation through e-mail. The facilities consist of a private consultation room with measurement equipment calibrated for use at relevant timelines and a waiting room area. Multimedia Appendix 2 describes all the included variables, definitions, categories, and sources for both assessments and explaining variables. No data from the participant records are obtained directly, and they are obtained only indirectly through registrations in national registers.

#### Clinical Assessments

Weight and HbA_1c_ are measured by the health coach using standard and validated measurement equipment (Tanita BC 420 S MA). Height, waist circumference, and hip circumference are measured, and BMI is calculated from the measured weight and height.

#### Lifestyle Assessment

QOL is measured through a validated questionnaire instrument (12-item Short Form Survey [SF-12]) [33].

#### Health Economic and Long-Term Assessments

Health care service usage, pharmaceutical consumption, and consumption of municipal care services, as well as morbidity status and mortality are measured through register data. Data from the Danish National Participant Register [34], the Danish National Prescription Registry [35], the Danish National Health Service Register [36], the Danish Civil Registration System [37], and relevant municipal statements and registers will be linked. Data linkage between registers is possible using the unique Danish Personal Identiﬁcation Number, which is assigned to each Danish citizen and applied throughout the public and private sectors [37]. Productivity loss is evaluated through a questionnaire (Multimedia Appendix 2) [38].

#### Explaining Variables

Each participant’s sociodemographic characteristics are obtained at the baseline face-to-face meeting and registered by the health coach. The explaining variables are used in the descriptive analyses of associations between the participants’ characteristics and the success of using LIVA 2.0.

### Health Economic Design

Within the scope of a cost-effectiveness analysis, expenditures related to the intervention, including acquisition, deployment, and operational costs, are compared with outcomes of the intervention in relation to the defined assessments. The cost effectiveness of the intervention is primarily assessed from the perspectives of the municipalities. The total cost of the intervention paid by a Danish municipality consists of investment costs as well as operating costs. Investment costs include expenditure for the training of health professionals as well as basic preparation cost. Operating costs cover the annual license fees for the individuals participating in the intervention as well as the individuals in the 1-year retention period. It is assumed that after 1 year in the intervention, participants will move to the retention period, where they will remain for 1 year; however, every year, 20% of the initial population will ultimately leave the intervention. Additionally, the operating costs include the salaries of the health professionals. The costs are compared to the effect of the intervention to evaluate cost effectiveness both in relation to the clinical effect and QOL [39].

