### Intervention

Participants in the intervention group receive login information for LIVA 2.0 at the first personal face-to-face meeting (either physical or digital), after which the health coach introduces the LIVA 2.0 app. After the first personal meeting, the same health coach will be coaching the participant throughout the period. When a health coach is on vacation or is sick for a short period, coaching is postponed. If the health coach is sick for a long period, a personal meeting with a new health coach is arranged to secure a personal relationship, after which the new health coach will be coaching the participant for the rest of the period. Based on our experiences from earlier studies, a half-time health coach can manage between 200 and 250 individuals. The participant and health coach together agree on goals for diet, physical exercise, sleep, and all other life areas of relevance to the participant. All goals are participant driven on the basis of the initial motivational interview with the health coach. The health coach is required to identify what health initiatives will benefit the participant the most based on the participant’s own wishes and to find out what is possible for the participant taking into account the participant’s personal barriers and facilitators. Using the app, the participant provides a daily record and also enters comments, concerns, and questions for the health coach, who can see the entire profile of the participant. The health coach provides individual asynchronous online consultation according to the participant’s needs and based on the participant’s registrations. The health coach encourages and praises goal attainment and endeavors to keep the participant motivated. Additionally, the health coach provides advice related to setting goals based on the SMART model (specific, measurable, attainable, relevant, and timely) [29] according to a predefined guideline structure (Table 1) [27,29].

**Table 1 table1:** Template of the Intervention Description and Replication checklist [30] for the eHealth lifestyle coaching tool (LIVA 2.0).

Item	Description

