Coaching approach	Individually delivered via the app or web-based delivery.
Coaching location	Initial personal meetings in municipality health centers, general practice medical centers, or the research unit for general practice at the University of Southern Denmark or over the internet, and then, solely web-based delivery.
Coaching time and quantity	The initial consultation with a health coach is estimated to last for approximately 45-60 minutes. The subsequent asynchronous eHealth coaching sessions are carried out once a week in the first 6 months and then every month for the last 6 months for maintenance. Thereafter, the participant could receive two eHealth coaching sessions and use LIVA 2.0 as a personal BCT tool (BCT: use of follow-up prompts).
Tailoring	Every participant receives personalized eHealth coaching sessions from their designated health coach. The provided feedback is based on the participant’s inputs on LIVA 2.0.

^a^BCT: behavior change technique.

^b^CALO-RE: Coventry, Aberdeen and LOndon-REfined taxonomy [31].

Asynchronous online consultations are held weekly during the first 6 months. Thereafter, online consultations are held monthly over a period of 6 months. After 12 months, the participants enter a retention period for 12 months, where the health coach will follow the participants’ registrations and may provide up to a maximum of four coaching sessions during that year. We expect that approximately 20% of participants will not be ready for retention after 1 year and these participants will be offered yet another year of intervention. This evaluation is performed by the health coach. The health coach endeavors to maintain participation through phone calls, text messages, and, if necessary, face-to-face meetings to prevent drop out*.* After 24 months of follow-up, participants are followed through national registers for long-term follow-up on a number of predefined endpoints. Participants in the intervention group receive the standard municipal preventive care service, such as diabetes education, to the extent that municipalities normally provide these care services throughout the observation period.

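### The costing path sends participants to retention after year 1 and has no branch for the roughly 20% expected to be offered a second intervention year; if coaching is costed from it, year-2 coaching is understated

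*Protocol article*

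**What the plan says.** All of this is in the protocol article.

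- **Health Economic Design, path:** "It is assumed that after 1 year in the intervention, participants will move to the retention period, where they will remain for 1 year". The same sentence adds that "every year, 20% of the initial population will ultimately leave the intervention".
- **Health Economic Design, cost items:** "Operating costs cover the annual license fees for the individuals participating in the intervention as well as the individuals in the 1-year retention period". After the path has been stated, a further sentence adds that "the operating costs include the salaries of the health professionals". No fee or salary amounts are given.
- **Intervention, text after Table 1:** the expectation is that "approximately 20% of participants will not be ready for retention after 1 year and these participants will be offered yet another year of intervention". The health coach decides who is in this group. Retention-year coaching is capped at four sessions.
- **Intervention, Table 1 (coaching time and quantity):** eHealth coaching takes place "once a week in the first 6 months and then every month for the last 6 months". For the time after that: "Thereafter, the participant could receive two eHealth coaching sessions".

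Cost-effectiveness in a municipal setting is the third aim in the Introduction and a tertiary outcome in the Abstract.

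**The concern.** The two sections describe different second years. In the costing path, a participant at month 12 either moves to low-intensity retention or has left. In the planned programme there is a third group of about 20% who are offered a further year of active coaching. The 20% who leave in the costing path cannot stand in for them, because leavers use no more coaching and repeaters use more than anyone in retention.

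What is at stake is the match between cost and effect. Participants are measured at 24 months and analysed by intention to treat, so any benefit of a second coaching year counts in the 24-month effect. If cost follows the assumed path, the coaching that produced that benefit is priced as retention. That would favour the intervention, and a municipality planning from the path would allow too little coaching for year 2.

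**Working it through.** The article states no cost figure, so there is nothing to reproduce. Coaching sessions are used as a proxy for coaching cost, with every session counted as equal.

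**Inputs from the article**
- Intervention arm: 200 participants.
- Intervention year: 26 weekly + 6 monthly = 32 sessions per person.
- Retention year: r = 2 (Table 1) or r = 4 (the maximum in the text).
- Share offered a repeat year: about 20%.
- Leavers: 20% of the initial population per year.

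**Assumptions not in the article**
- Uptake of the offer: 50-100%.
- Repeat-year sessions: e = 12 (monthly only) to 32 (full schedule again).
- Leavers before year 2: 0 or 20%, so n = 200 or 160 people in year 2.
- The 20% offered a repeat year is taken either of all 200 or of those still in the programme.

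**Formulas**, with k the number who repeat:
- Year 2, assumed path = n × r
- Year 2 with repeats = (n − k) × r + k × e
- Two-year total = 200 × 32 + year 2 = 6,400 + year 2

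| n | k | e | r | Year 2 assumed | Year 2 with repeats | Ratio | Two-year total | Change |
|---|---|---|---|---|---|---|---|---|
| 160 | 16 | 12 | 4 | 640 | 768 | 1.2 | 7,040 to 7,168 | +1.8% |
| 160 | 20 | 32 | 4 | 640 | 1,200 | 1.88 | 7,040 to 7,600 | +8.0% |
| 200 | 40 | 32 | 4 | 800 | 1,920 | 2.4 | 7,200 to 8,320 | +15.6% |
| 160 | 40 | 32 | 4 | 640 | 1,760 | 2.75 | 7,040 to 8,160 | +15.9% |
| 200 | 40 | 32 | 2 | 400 | 1,600 | 4.0 | 6,800 to 8,000 | +17.6% |
| 160 | 40 | 32 | 2 | 320 | 1,520 | 4.75 | 6,720 to 7,920 | +17.9% |

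The first row is the mildest combination: half of 20% of 160 stayers is 16 people, repeating at monthly intensity. The last row is the strongest: 240 + 1,280 = 1,520 sessions against 320.

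The choice of denominator matters. Against the assumed year 2 the gap can be large (up to 4.75 times). Against two years it is modest, because the 6,400 first-year sessions dominate.

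**What the two-year percentages leave out.** The base gives all 200 people a full first year. The section on prevention of drop-out expects about 15% to leave in the first two weeks: 0.15 × 200 = 30 people, each with about 30 sessions not delivered, or about 900 sessions. That is comparable to the 128 to 1,200 sessions added here and works in the opposite direction on the two-year total. The percentages therefore isolate one omission and are not the net error of the path.

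**The case against.** **The path is not expressly tied to salaries.** The assumption follows directly on the licence-fee sentence, and salaries come afterwards as a separate item. Coaching is where the direction is clear, yet the text does not say that coaching cost is derived from the path. Licences are where the path most naturally applies, yet no direction can be shown there without fees. This stands, and it is why the conclusion is conditional.

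**The cost items are wide enough to hold repeaters.** Licences for people in the intervention and coach salaries would both include repeaters if observed use is costed, and then nothing is understated. This also stands. The section does not say that observed use will be costed, however, and what it does state is an assumption that differs from the programme.

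**Sessions are not coach time.** Coaches also follow registrations during retention, and the personal meetings are not counted. One might turn to staffing instead, since "a half-time health coach can manage between 200 and 250 individuals": 40 × 0.5/250 = 0.08 to 40 × 0.5/200 = 0.10 full-time posts for 40 repeaters. That holds only if the stated caseload is made up of people in the intervention phase, which the article does not say. If it mixes phases, repeaters add nothing by this measure, so the conclusion does not rest on it.

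**A condensed article leaves such detail to a fuller plan.** That is fair for sensitivity ranges and model structure. It does not cover two statements in the same article that disagree.

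**A stronger reading.** A reader might infer that the programme's total cost is understated, or that the cost-effectiveness result will be wrong in the intervention's favour. The documents do not support that. No unit costs are given, the licence direction is unknown, early drop-out works the other way on the two-year total, and the article does not show that the path will drive the salary cost.

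**Conclusion.** The inconsistency is real: the stated costing path does not describe the planned programme, and its 20% leavers are not the 20% expected to be offered a repeat year. Its consequence is conditional. If coaching cost is derived from the path, year-2 coaching is understated, by a factor between the mildest and strongest rows of the table, while the two-year total moves only modestly. The width of the range comes mainly from uptake and repeat-year intensity, which the article does not give.

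Neither a money amount nor a change in the cost-effectiveness ratio can be computed. The point is minor. It deserves correction because it concerns a stated assumption that feeds a stated aim.

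**What to change.** In Health Economic Design, replace the assumed path with each intervention participant's actual time in intervention and in retention, applied to both licences and coaching and including any second intervention year. If a modelled path is preferred, keep it and add a second-year intervention branch of up to about 20%, separate from the 20% who leave.

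The cost is a change of wording and slightly more analysis work, with no new participants or visits. The cost-effectiveness result may become less favourable to the intervention.

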### Analysis Strategy

All data are analyzed according to the intention-to-treat principle [43]. Analyses are mainly carried out according to the two target groups. However, stratification according to participant characteristics and user experiences is applied to investigate associations between success and the different characteristics. Ordinary least square regression and difference between groups over time are used to explore significant associations. Statistical significance is inferred at a two-tailed *P* value <.05. Robust standard errors are calculated. Data are analyzed by experts in biostatistics. After the study, all data will be made accessible on request in anonymized form to allow full peer scrutiny and facilitate secondary research.

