### Sample Size Considerations

The primary objective of this study is the measurement of changes in body weight and waist circumference. Based on a recent study by Haste et al, which evaluated a web-based weight loss intervention among men with diabetes, we expect a weight loss of at least 4.5 kg at 12 months in the intervention group as compared with 2.5 kg in the control group [8] (Textbox 2).

Sample size calculation.A power calculation based on standard deviations observed in the study [8] shows that the detection of a difference in weight loss of 2.0 kg with a power of 0.95% requires 55 participants in the intervention group and 32 in the control group. To allow for drop out according to the experienced attrition rates in the same study [8] (39% of participants in the intervention group and 57% in the control group are expected to drop out at 12 months), we will recruit 100 participants in the intervention group and 70 in the control group (Figure 1). To be able to stratify analyses according to obese participants at risk of developing chronic diseases and obese participants with diabetes, we will recruit 100 obese participants at risk of developing chronic diseases and 100 obese participants with diabetes. Therefore, in total, we will consider 200 participants in the intervention group and 140 in the control group.

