### Prevention of Drop Out and Loss to Follow-Up

Based on prior experience, approximately 15% of participants will drop out during the first 2 weeks owing to technological challenges, etc. Likewise, after 3 months, approximately 20% of participants will lose motivation and be less active on the platform [8]. The coach will endeavor to maintain participation through phone calls, text messages, and, if necessary, face-to-face meetings. In the case of exclusion before the end of the trial (eg, due to pregnancy), the participant will be asked to complete a final questionnaire and have objective parameters measured in order to provide data for the intention-to-treat analysis.

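### The cost model assumes that 20% of participants leave the intervention each year; this is not reconciled with the protocol's other drop-out figures, although actual participation will be observed

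*Protocol article*

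**What the plan says.** The Health Economic Design section builds the municipality's cost from investment costs and operating costs. Operating costs are annual licence fees, for people in the intervention and in the retention year, plus health professionals' salaries. Between these two components it states that participants move to a one-year retention period after year 1, but that "every year, 20% of the initial population will ultimately leave the intervention".

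Three other places describe how participation or follow-up is expected to develop:

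- Sample Size Considerations: "39% of participants in the intervention group and 57% in the control group are expected to drop out at 12 months". The rates come from an earlier trial and are used to set recruitment ("To allow for drop out according to the experienced attrition rates in the same study").
- Prevention of Drop Out and Loss to Follow-Up: "approximately 15% of participants will drop out during the first 2 weeks", put down to technological difficulties among other things. About 20% are then expected to be less active on the platform after 3 months.
- Intervention: about 20% are expected not to be ready for retention after a year and will be offered a second year of intervention.

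The Abstract lists retention rate among the tertiary outcomes and says that individual platform data will be combined with the clinical data. The Analysis Strategy section applies intention to treat to all data.

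**The concern.** Cost-effectiveness in a municipal setting is the third stated aim. Licence and salary costs depend on how many people are on the programme and for how long, so the assumed course of participation is a main driver of operating cost. The article fixes that course with one unsupported figure, while other sections give a higher 12-month figure, an early loss, and a group who stay in full intervention for a second year. It does not say how these fit together.

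The trial will also record participation directly. If costs follow an assumed course while the effect comes from the people actually randomised, cost and effect may describe different patterns of exposure, and their ratio becomes hard to interpret.

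**Working it through.** **The plan's own use of the 39%.** The sample-size text says the calculation "requires 55 participants in the intervention group and 32 in the control group", and then "we will recruit 100 participants in the intervention group and 70 in the control group". Dividing by the expected completion fraction gives 55 / (1 − 0.39) = 90.2, so 91, and 32 / (1 − 0.57) = 74.4, so 75. The stated 100 and 70 are not reproduced. The printed rates were therefore not applied exactly, but 39% is still the article's stated 12-month expectation for the intervention group.

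**Inputs for the comparison.** Intervention group 200; exit 20% of the initial population per year (Health Economic Design); drop-out 39% at 12 months (Sample Size Considerations); early drop-out 15% by week 2 (Prevention of Drop Out). Assumption for every step below: leaving the intervention and dropping out are the same event. The article does not say so.

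**Month 12.**

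- Cost assumption: 200 × (1 − 0.20) = 160.
- Sample-size assumption: 200 × (1 − 0.39) = 122.
- Ratio: 160 / 122 = 1.31, a gap of 38 people or 19 percentage points.

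The cost assumption reaches 200 × (1 − 0.40) = 120 only at month 24.

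**Average over year 1** (relevant because cost accrues through the year; the timing of exit is my assumption).

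- Cost assumption, linear exit: (1 + 0.80) / 2 = 0.90.
- 39% exit, linear: (1 + 0.61) / 2 = 0.805; 0.90 / 0.805 = 1.12.
- 15% gone at week 2, then linear to 61%: (2/52) × 1 + (50/52) × (0.85 + 0.61) / 2 = 0.740; 0.90 / 0.740 = 1.22.

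The average excess is thus about 12% to 22%, not 31%.

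**The early figure alone.** A 15% loss by week 2 is 15 / 20 = 75% of the whole first-year exit in the cost assumption. If the later 20% who are less active were also counted as gone, which the text does not say, 0.85 − 0.20 = 0.65 or 0.85 × 0.80 = 0.68 would remain. The ratios are 0.80 / 0.65 = 1.23 and 0.80 / 0.68 = 1.18.

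**Second intervention year.** Twenty per cent of 200, 160 or 122 people is 40, 32 or 24. The economic text moves participants to retention after year 1 and mentions no such group.

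**Direction.** Three conditional cases at month 12:

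- The effect is estimated separately and only operating cost follows headcount: the larger headcount raises modelled cost, which counts against LIVA 2.0.
- Cost and benefit both scale with headcount: the 160 or 122 cancels and cost per kg does not change.
- Cost is fixed and 4.5 kg is credited to each person remaining: 160 × 4.5 = 720 kg against 122 × 4.5 = 549 kg. Since 549 / 720 = 0.76, cost per kg looks 24% lower.

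The article does not say which case applies.

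**The case against.** The strongest reply is that 20% and 39% measure different things. The 39% is attrition from an earlier trial, used to size recruitment. It stands beside 57% for a control group that has no platform to leave, so it reads most naturally as loss to the 12-month assessment. The section on preventing drop-out also separates the two events, since participants excluded early are still to be measured for the intention-to-treat analysis. The 20% is exit from a programme that a municipality pays for. This stands: the documents do not show the figures to be the same quantity, and 39% has no better claim than 20% to be the base case.

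The reply is weaker against the 15% in the first 2 weeks. That figure is put down to technological problems and is followed by a remark on platform activity, so it looks like programme use. The 20% who become less active, however, have not been said to leave.

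A reader might infer that year-1 participation is overstated by a third, or that cost per kg is made to look 24% too favourable. Neither is supported. The first holds only at month 12 and only if the terms coincide. The second holds cost fixed although licences and salaries follow participation, and nothing in the article credits 4.5 kg to a modelled 80%. Effect estimation by intention to treat is already the stated principle.

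Finally, a condensed article may leave sensitivity ranges to a fuller plan. That is fair, so the point rests on the assumption the article does fix.

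**Conclusion.** The concern holds in a limited form. The article bases operating costs on an assumed exit rate for which it gives no basis. It does not relate that rate to its other expectations about drop-out and a second intervention year, and it does not use the participation data the trial will hold. If the terms mean the same event, the month-12 headcount differs by a factor of 1.31, and average year-1 participation by about 12% to 22% under the timings tried. If they mean different events, the size is unknown and the missing definition is itself the gap. No direction of bias in cost-effectiveness can be claimed. The weight-loss and HbA1c analyses are unaffected.

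**What to change.** In the base case, cost licences and coach salaries from each randomised LIVA 2.0 participant's observed platform time, coaching sessions and any second intervention year. As licence fees are annual, state how time on the platform is converted into licence years. Set these costs against the intention-to-treat effect in the same randomised population.

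Keep 20% per year only as a scenario value, within a sensitivity range that reaches 39% at 12 months. Define leaving the intervention separately from dropping out of the trial, and report both. Reconcile the assumption that participants move to retention after year 1 with the group expected to be offered another intervention year.

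The cost is revised wording in the economic analysis and slightly more analysis work. Platform data are already to be combined with the trial data. The cost-effectiveness figure could become less favourable.
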